## Abstract

**Background:**

Laparoscopy training has become an integral part of surgical education. Suturing and knot tying is a basic, yet inherent part of many laparoscopic operations, and should be mastered prior to operating on patients. One common and standardized suturing technique is the C-loop technique. In the standard training setting, on a box trainer, the trainee learns the psychomotor movements of the task and the laparoscopic visuospatial orientation simultaneously. Learning the psychomotor and visuospatial skills separately and sequentially may offer a more time-efficient alternative to the current standard of training.

**Methods:**

This is a monocentric, two-arm randomized controlled trial. The participants are medical students in their clinical years (third to sixth year) at Heidelberg University who have not previously partaken in a laparoscopic training course lasting more than 2 hours. A total of 54 students are randomized into one of two arms in a 1:1 ratio to sequential learning (group 1) or control (group 2). Both groups receive a standardized introduction to the training center, laparoscopic instruments, and C-loop technique. Group 1 learn the C-loop using a transparent shoebox, thus only learning the psychomotor skills. Once they reach proficiency, they then perform the same knot tying procedure on a box trainer with standard laparoscopic view, where they combine their psychomotor skills with the visuospatial orientation inherent to laparoscopy. Group 2 learn the C-loop using solely a box trainer with standard laparoscopic view until they reach proficiency. Trainees work in pairs and time is recorded for each attempt. The primary outcome is mean total training time for each group. Secondary endpoints include procedural and knot quality subscore differences. Tertiary endpoints include studying the influence of gender and video game experience on performance.

**Discussion:**

This study addresses whether the learning of the psychomotor and visuospatial aspects of laparoscopic suturing and knot tying is optimal sequentially or simultaneously, by assessing total training time, procedural, and knot quality differences between the two groups. It will improve the efficiency of future laparoscopic suturing courses and may serve as an indicator for laparoscopic training in a broader context, i.e., not only for suturing and knot tying.

**Trial registration:**

This trial was registered on 12 August 2015 with the trial registration number DRKS00008668.

## Background

Minimally invasive surgery (MIS) involves learning a separate skill set from that of open surgery. Although some of the necessary qualities are the same, e.g., bimanual dexterity and steadiness, many of the basic skills must be learned for the first time or anew, e.g., the fulcrum effect, tissue grasping, needle manipulation, knot tying, etc. These basic psychomotor skills give surgeons the tools necessary to complete full operations; therefore, the learning of them has become one of the cornerstones of laparoscopic training curricula [1–3]. As many surgical operations defer to the laparoscopic approach, it has become imperative for surgical trainees to demonstrate proficiency in basic and procedural skills prior to operating on patients. Training modalities, e.g., virtual reality (VR) simulators, inanimate box trainers, and cadaveric organ trainers can be used as a safe, ethical, and effective means to do this [4–8].

Box trainers provide a realistic platform for the learning of laparoscopic skills with real instruments [9]. Intracorporeal suturing and knot tying [10] is an invaluable skill needed for minimally invasive operations [11, 12]. Suturing skills learned via a box trainer suture model have been shown to transfer to the operating room (OR) [13]. Training within the box trainer familiarizes trainees with the two major facets of laparoscopy: psychomotor control and visuospatial orientation [14–18].

Surgeons need to be familiar with depth perception and 2D–3D visuospatial understanding, since laparoscopy utilizes an indirect view. However, it remains to be determined if the learning of psychomotor and visuospatial skills simultaneously is optimal, as in a box trainer. Learning these two skills separately and sequentially may offer a more effective training alternative that reduces the learning or teaching time for trainees and mentors respectively. This would lower the workload of tutors and the learning curve of trainees, and save limited time and resources in a training center. Therefore, we aim to explore whether sequential learning with a transparent shoebox, where one learns the psychomotor movements, followed by training on a box trainer with the indirect laparoscopic view, expedites the learning of the surgical C-loop technique in comparison to training solely on a box trainer with the indirect laparoscopic view, where one learns the psychomotor and visuospatial skills simultaneously.

## Methods

### Objective

The primary goal of this study is to identify if students in group 1, who learn the surgical C-loop technique using a transparent shoebox before using a box trainer with laparoscopic view, have a shorter learning curve than students in group 2, who learn the technique using solely a box trainer with laparoscopic view (Fig. 1). Secondary endpoints include number of attempts taken to gain proficiency, and examining procedural and knot quality subscore differences. In subgroup analyses we will separately explore possible gender differences and influence of previous video game experience on training time, number of attempts needed to reach proficiency and knot quality respectively.

**Fig. 1 Fig1:**
[figure not shown]
Study flowchart

### Study design

This is a registered prospective, single-center, two-arm, parallel group randomized controlled trial.

### Setting and participants

This study is conducted in the MIS training center of Heidelberg University Hospital’s Department of General, Visceral, and Transplantation Surgery. It offers a voluntary laparoscopic training course to medical students. Training tutors are specially trained medical students (*n* = 4) at Heidelberg University, non-blinded to the training groups, who receive a standardized rater training prior to the beginning of data collection.

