### Training curriculum

The sequential learning group (group 1) learn the psychomotor aspects of laparoscopic suturing and knot tying first on the transparent shoebox without having to adjust to the visuospatial orientation inherent to the laparoscopic view of a box trainer. Once they reach the predefined proficiency criteria explained below (Tables 1, 2 and 3), these students then train on the box trainer with laparoscopic view until proficient (Fig. 2). The control group (group 2) learn the psychomotor skills and visuospatial aspects of laparoscopy simultaneously, as is traditionally done. They train using the box trainer with laparoscopic view until proficient in the predefined criteria. Specially trained peer tutors assist trainees during the course of the study and are available on demand in the training room for both groups; this has proven to be beneficial to trainee learning [19].

**Table 1 Tab1:** Procedural proficiency checklist

Procedure assessment			Yes/No
Needle position 1	1	Held at one half to two thirds distance from the tip	
	2	Angle 90° ± 20°	
	3	Uses tissue or other instrument for stability	
	4	Attempts at positioning (≤3)	
Needle driving 1 (entry to incision)	5	Entry at 60° to 90° to the tissue plane	
	6	Driving with one movement	
	7	Single point of entry through the tissue	
	8	Removes the needle along its curve	
Needle position 2	9	Held at one half to two thirds distance from the tip	
	10	Angle 90° ± 20°	
	11	Uses tissue or other instrument for stability	
	12	Attempts at positioning (≤3)	
Needle driving 2 (incision to exit)	13	Driving with one movement	
	14	Removes the needle along its curve	
Pulling the suture	15	Needle on needle holder in view at all times	
	16	Uses the pulley concept	
Technique of knots	17	Correct C-loop (no S- or O-loops)	
	18	Smoothly executed throw, no fumbles	
	19	Correct inverse C-loop (no S- or O-loops)	
	20	Smoothly executed throw, no fumbles	
	21	Knot squared (capsized/reef/surgical)	
	22	Correct third C-loop (no S- or O-loops)	
	23	Smoothly executed throw, no fumbles	
Total points

**Table 2 Tab2:** Knot quality checklist

Knot quality assessment	Available points
No visible gaps between stacked throws	1
Knot tight at base	1
Only edges are opposed (no extra tissue in knot, e.g., back wall)	1
Knot holds under tension	2
Maximum	5

**Table 3 Tab3:** Competency checklist

Competency assessment	Goal	Yes/No
Time (min:sec)	≤01:15	
Procedure	≥18	
Knot quality	≥4	
Accuracy (mm)	≤2	
Competency (if all “Yes” above)

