**Fig. 3 Fig3:**
[figure not shown]
Standardized silicone suture pad

Training pairs are required to rate each other throughout the training process until they reach the predefined competency levels for knot quality, suture position, and time. Procedural competency is assessed using a previously validated modified 23-point implementation checklist [14] (Table 1), originally published by Munz et al. [29].

Knot quality is scored using a 5-point scale designed by Muresan et al. [10], which assesses a knot’s throws, tightness, edge opposition, and ability to hold under tension (Table 2). Furthermore, accuracy is recorded by measuring the distance (mm) of the stitch from the edge of the entry and exit points of the standardized suture pad. Operative time is also recorded.

A trainee demonstrates competency for the C-loop upon finishing it in ≤01:15 (min:sec), attaining ≥18 points on the procedural implementation checklist, scoring ≥4 on the knot quality scale, and maintaining stitching ≤2 mm from the edge of the suture pad’s entry and exit points (Table 3). According to the available medical literature, experienced surgeons (expert level) reach these goals for the surgical C-loop [14]. Once a student has reached competency according to his or her training partner, a specially trained peer tutor is asked to provide expert assessment. If the participant then performs a C-loop, attaining the aforementioned competency criteria under supervision of the tutor, he or she is considered proficient in the technique; thus proficiency is achieved once a trainee completes the C-loop suturing technique on two consecutive occasions with the predefined competency criteria – once for the partner and once for the peer tutor assessment.

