### Primary endpoint

The primary endpoint is total training time needed to reach proficiency in a predefined standardized suturing and knot tying technique.

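### The pass that stops the primary-endpoint clock is given by tutors who know the arm and also assist the trainees; no masked rating is described, and the size of any bias cannot be stated

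*Protocol article*

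**What the plan says.** All references are to the protocol article, Methods.

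- Setting and participants: there are four student tutors, "non-blinded to the training groups, who receive a standardized rater training prior to the beginning of data collection".
- Training curriculum, on the tutors' other role: "Specially trained peer tutors assist trainees during the course of the study and are available on demand in the training room for both groups".
- Training curriculum, text after Figure 3: once the training partner judges a trainee competent, "a specially trained peer tutor is asked to provide expert assessment". Proficiency needs two consecutive passes, "once for the partner and once for the peer tutor assessment".
- Same place and Table 3: a pass requires a time of at most 01:15, stitches within 2 mm of the marked points, and "attaining ≥18 points on the procedural implementation checklist, scoring ≥4 on the knot quality scale".
- Primary endpoint: "The primary endpoint is total training time needed to reach proficiency in a predefined standardized suturing and knot tying technique".
- Training curriculum, on group 1: after reaching proficiency on the shoebox, "these students then train on the box trainer with laparoscopic view until proficient". Group 1 therefore has two proficiency tests and group 2 has one. The last test is on the box trainer in both arms.

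**The concern.** The primary endpoint is a time that ends at a rater's decision. That rater knows the allocation and may have coached the trainee. If knowledge of the arm made tutors a little more lenient or more strict in one arm, training time in that arm would shift even with no real difference in learning. The shift would enter the primary comparison directly, and the t test could not tell it from a training effect.

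Rater training improves consistency between raters but does not remove their knowledge of the arm. The partner's rating gives no independent check, because the partner watches the trainee on the device that defines the arm.

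**Working it through.** **1. The chain.** Tutors are non-blinded (Setting and participants). They assist trainees in both groups (Training curriculum). A tutor's pass completes proficiency (Training curriculum, after Figure 3). Time to proficiency is the primary endpoint (Primary endpoint). Each link is stated, and no masked, independent or duplicate rating of the pass is described.

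**2. Where the leeway lies.** Two of the four criteria, time and accuracy in mm, are measured. The other two are scores.
- Procedure (Table 1): by my count at least 12 of the 23 items depend on the rater's eye. Seven concern fluency or needle path (items 6, 8, 13, 14, 18, 20, 23; for example "Smoothly executed throw, no fumbles"). Five concern an estimated angle or grip position (items 1, 2, 5, 9, 10). A trainee who earns the other 23 − 12 = 11 points needs 18 − 11 = 7 of these 12. Near the cut-off a single item decides.
- Knot quality (Table 2): the tension item carries 2 of 5 points. Losing it leaves at most 3, below the cut-off of 4, so it decides the result alone.

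**3. The plan's own sample size.** Inputs from Sample size determination: difference 15 s, SDs 15.6 s and 22.2 s, two-sided α = 0.05, power 0.80.
- Root-mean-square SD = √[(15.6² + 22.2²)/2] = √368.1 = 19.19 s.
- The normal approximation gives 26 per group. The noncentral t gives power 0.789 at 26 and 0.805 at 27 (Welch: 0.788 and 0.803).
- The stated 27 per group is reproduced.

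**4. What a shift would do if those seconds are taken at face value.** The shifts are assumed; the calculation is Welch noncentral t with 27 per group.

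| Assumed arm-dependent shift | Rejection rate, no true difference | Power, true 15 s, shift against it |
|---|---|---|
| 0 s | 5% | 80% |
| 2 s | 6.6% | 68% |
| 5 s | 15.5% | 47% |
| 7.5 s | 29% | 29% |

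If tutor-rated attempts passed with assumed probability 0.7 in one arm and 0.8 in the other, expected tutor attempts would differ by 1/0.7 − 1/0.8 = 0.179. At 75 s each that is about 13 s.

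Counted in trainees, the design difference is 27 × 15 = 405 s. That equals 405/75 = 5.4 extra attempts, or 405/150 = 2.7 refusals if each costs two attempts under the consecutive-pass rule. Both assume attempts near the 75 s limit.

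**5. Why that scale is doubtful.** The two passing attempts alone may take up to 150 s, and group 1 passes two proficiency tests. One 75 s attempt equals 75/15.6 = 4.8 SDs in group 1 and 75/22.2 = 3.4 SDs in group 2. SDs this small would require nearly all trainees in an arm to need about the same number of attempts. That is hard to reconcile with a total over repeated attempts by novices.

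**6. The same sums if the unit were minutes (an assumption).** 27 × 15 × 60 = 24,300 s. That is 24,300/75 = 324 one-attempt refusals (12 per trainee) or 24,300/150 = 162 two-attempt refusals (6 per trainee). One extra attempt per trainee would be 75/900 = 1/12 of the design difference, against 75/15 = 5 times it on the seconds scale.

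**The case against.** The strongest case on the other side has four parts.

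- **Safeguards exist.** All four criteria must be met. Two are measured, the checklists are published with fixed cut-offs, tutors are trained as raters, and a partner's pass must come first. This stands. A tutor's discretion matters only for attempts that already meet the time and accuracy limits. The safeguards narrow the exposure but do not mask the rating.
- **There is no evidence of bias.** This stands. A reader might infer from the Discussion that the trial team expects group 1 to win and that tutors would favour it. The Discussion expects faster learning on the shoebox, but says that transfer to the box trainer is still to be determined. It therefore supports an expectation for the shoebox phase only.
- **The size is unknown.** This stands. A reader might infer that about three to six biased sign-offs would create or cancel the design difference. That holds only if the 15 s really is a difference in total training time.
- **Masked re-scoring is an incomplete remedy.** This stands. Training stops at the live pass. If a masked score rejects that pass, no later attempt exists, so a first masked pass is undefined. Video cannot show whether a knot holds under tension. The article does not say that the box-trainer image can be recorded or what it shows. The shoebox sign-off, which only group 1 has, stays unmasked. By Trial status, recruitment began in April 2015, so sign-offs already completed cannot be recorded.

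None of this removes the stated chain from unblinded tutor to primary endpoint.

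**Conclusion.** The point holds as a documented exposure, not as a demonstrated bias. A tutor who knows the arm and may have coached the trainee gives the pass that ends the primary endpoint. The article describes no masked check on that decision. The leeway is confined to the procedure checklist and the knot score.

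The size cannot be stated. It could equal the whole design difference if the seconds in Sample size determination are total training time, or be slight if the quantity or unit is something else. The assumed shifts and pass probabilities illustrate this range; they are not estimates. The design weakness itself does not depend on the scale.

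It is worth correcting because a partial remedy is cheap. It does not by itself invalidate the trial.

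**What to change.** 1. For the box-trainer sign-off, which is the same task in both arms, have the pass decided by one of the four existing tutors who did not coach that pair and, where possible, is not told the arm. Without concealment of the arm this separates coaching from assessment but does not mask.
2. Where the box-trainer image can be recorded, record every further sign-off attempt in both arms, passed or failed. Have an existing non-coaching tutor re-score the items visible on video without arm information, and leave the tension item to the live rating. Report agreement between masked and live ratings by arm.
3. If a sensitivity analysis of the primary endpoint is added, treat a live pass that the masked score does not confirm as censored at that time. The comparison then needs a method for censored times instead of the t test.
4. State as a limitation that group 1's shoebox sign-off, and sign-offs already completed in either arm, remain unmasked.

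Cost: protocol wording, some scheduling so that a non-coaching tutor is available (to be confirmed with only four tutors), and scoring time for clips of about 75 s. No extra staff are needed. Protection is partial.

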### Inclusion and exclusion criteria

The inclusion criterion mandates that participants are medical students in their clinical years (third to sixth year) at Heidelberg University. Exclusion criteria include students who have previously participated in a laparoscopic training course of more than 2 hours duration or who had training in laparoscopic surgery in the OR.

### Video introduction to laparoscopic suturing and knot tying

All students receive a standardized video-based introduction to the suturing and knot tying technique at the start of the study. Students may refer to this video throughout the course of their participation.

### Introduction to the training modalities in the training center

Trained student tutors provide a standardized introduction for the box trainer, shoebox, and laparoscopic instruments, as well as instructions for their use. Students can, therefore, familiarize themselves with the training modalities, workspace, and terminology prior to the induction of their training.

### Randomization

Participants are randomly allocated to either the sequential learning group (group 1) or control group (group 2) in a 1:1 ratio. The randomization of subjects is performed by an employee otherwise not involved in the study using sealed envelopes labeled by block. Trainees are allocated to groups without stratification by gender or gaming experience. Although this study would benefit from a 1:1 ratio of men to women, this cannot be mandated since the data is collected through participation in a university elective course which is offered on a first-come-first-serve basis. Consequentially, we cannot explore outcome differences in heterogeneous or homogeneous groups, e.g., male-female, male-male, female-female, in a standardized manner; there may be an influencing factor that stems from the communication dynamic, previous experience of a partner, etc. We aim to explore these differences by comparing outcomes between pair group subgroup analysis following data acquisition. An employee of the Department of Medical Biometry at Heidelberg University, who is otherwise not involved with the training, tests, or data collection from the present study, assigned block randomization.

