**Fig. 2 Fig2:**
[figure not shown]
Transparent shoebox used by intervention group (left). Box trainer with laparoscopic view used by both groups (right)

Following randomization, participants are put into training pairs, which is a common practice within surgical training [20, 21]. This allows the trainees to give each other real-time competency assessment and feedback, which is motivational [22, 23], in addition to saving time for the trainers, and space in the training center. We recently explored the difference between laparoscopic training alone and in pairs and found there to be no distinction in outcome between the two groups (protocol, own data, unpublished). It has been shown that students – whether alone or in a collaborative pair – can learn as much by observing their peers learn a task as they can by performing the task themselves [24, 25]. This is known as vicarious learning, which typically does not provide for communication between the student being tutored and the student watching. It should be made clear that students in our training environment can communicate directly with one another, which may prove even more useful. Based on these grounds, we believe that the pragmatic aspect of saving time and resources in a busy training center outweighs the potentially confounding effect of partner training.

The student who is watching records the time taken for each attempt of the operating partner, starting from when the needle is grasped and ending once the final knot is tied. All attempts must be completed and the time per attempt must be recorded for each trainee. In the event of technical or instrument failure, e.g., the suture thread getting stuck in the grooves of the instrument, time is stopped and recorded, and “N/A” and a brief description of what happened are written next to the attempt. Rather than mass practice, we implement the more effective interval training [26–28]; trainees are required to switch positions at least every five completed knot attempts. Students train using two laparoscopic needle holders (KARL STORZ GmbH & Co. KG, Tuttlingen, Germany) and a standardized silicone suture pad with diagonal incisions and predefined suture entry and exit points (Fig. 3) (Big Bite Medical GmbH, Heidelberg). The suture material is a Polysorb 3-0 braided absorbable suture with a CV-23 taper ½ 17-mm needle (Covidien^TM^, Minneapolis, MN, USA).

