### Tertiary endpoints

Tertiary endpoints involve subanalyses of gender differences and the influence of video game experience. Surgery has traditionally been a male-dominated field and research has demonstrated that male medical students are faster at acquiring surgical skills and demonstrate superior visuospatial skills in comparison to their female peers [30–33]. We will explore this further by comparing male and female performance in both groups for total time taken and number of attempts. Furthermore, we will explore the influence of video game experience, in years, on total time taken and number of attempts, for both groups.

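### The planned comparison of pair types cannot separate a partner's influence from the trainee's own gender; compare trainees of the same gender instead

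*Protocol article*

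**What the plan says.** The Randomization section gives the motive for looking at pairs: "there may be an influencing factor that stems from the communication dynamic, previous experience of a partner, etc". It acknowledges a limit: "we cannot explore outcome differences in heterogeneous or homogeneous groups, e.g., male-female, male-male, female-female, in a standardized manner". It then states the method: "We aim to explore these differences by comparing outcomes between pair group subgroup analysis following data acquisition".

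Other parts of the protocol article bear on this:

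- **Allocation (Randomization):** "Trainees are allocated to groups without stratification by gender or gaming experience".
- **Pairing (Training curriculum):** "Following randomization, participants are put into training pairs". How partners are chosen is not stated.
- **Expected gender effect (Tertiary endpoints):** "research has demonstrated that male medical students are faster at acquiring surgical skills and demonstrate superior visuospatial skills". The direction is given but no size. The gender analysis is planned separately, as "comparing male and female performance in both groups for total time taken and number of attempts".
- **Tests (Statistical analysis):** subgroup analyses are descriptive, with Mann-Whitney U tests for continuous and Chi-square tests for categorical variables. No adjustment is mentioned.

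The article nowhere considers own gender and partner gender together.

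**The concern.** The question is about the partner, but the comparison is between kinds of pair. A male-male pair contains only men and a female-female pair only women, so a contrast between them is also a contrast between men and women. The protocol expects men to learn faster. On that premise male-male pairs will tend to look faster for a reason that has nothing to do with pairing.

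At stake is the interpretation of this one exploratory result: an ordinary gender difference could be reported as an effect of pair make-up. The separate male-female comparison would show a reader that a gender gap exists, but not how much of the pair contrast it explains.

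**Working it through.** **Inputs.** From the protocol: 54 trainees allocated 1:1, hence at most 27 pairs; the three pair types; unadjusted subgroup tests; men expected to be faster. Assumed, because the protocol gives neither: an own-gender gap *g* of 0 to 1.0 SD and a male share of 30 to 50%.

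**The plan's own figure.** None is given for the pair comparison. The overall size reproduces: SD = √((15.6² + 22.2²)/2) = 19.19 s. For a 15 s difference, two-sided 5% and 80% power, the t-based calculation gives 26.7, so 27 per group (power 80.5%). On that SD, 0.5 and 0.8 SD are 0.5 × 19.19 = 9.6 s and 0.8 × 19.19 = 15.4 s.

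**Expected means.** Let a woman with a female partner have mean *a*, let being male lower it by *g*, and let having a male partner lower it by *p*.

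- Female-female: *a*
- Mixed: average of (*a* − *p*) and (*a* − *g*), which is *a* − (*g* + *p*)/2
- Male-male: *a* − *g* − *p*

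Female-female minus male-male is *g* + *p*. All three means depend on *g* and *p* only through their sum, so they cannot separate the two. With *p* = 0 the difference is *g* in full and mixed pairs lie at the midpoint.

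With own gender fixed, men with a female partner minus men with a male partner is (*a* − *g*) − (*a* − *g* − *p*) = *p*. Women give the same: *a* − (*a* − *p*) = *p*.

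**Rejection rates with no partner effect.** Simulation of 27 randomly formed pairs, about 2,000 runs per setting, no arm effect and no within-pair correlation, nominal 5%. Cells give the results for 50 / 40 / 30% men.

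| Gap *g* (SD) | Three pair types, Kruskal-Wallis by trainee | Mixed vs same-gender, Mann-Whitney | Partner term, own gender in model |
|---|---|---|---|
| 0 | 4.4 / 5.1 / 4.1% | 5.0 / 4.9 / 5.2% | 4.8 / 5.8 / 5.3% |
| 0.2 | 6.8 / 5.6 / 5.5% | 4.4 / 5.5 / 4.5% | 5.2 / 5.5 / 5.1% |
| 0.5 | 16.1 / 14.7 / 12.7% | 5.1 / 6.2 / 7.0% | 5.6 / 4.7 / 4.5% |
| 0.8 | 37.6 / 34.6 / 30.7% | 4.8 / 7.7 / 11.5% | 4.6 / 5.5 / 4.2% |
| 1.0 | 50.3 / 49.2 / 41.5% | 5.5 / 8.5 / 15.4% | 5.8 / 4.5 / 4.7% |

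The simulated female-female minus male-male difference at 50% men was 0.50 SD for *g* = 0.5 and 0.80 SD for *g* = 0.8, as the algebra requires. Using pair means as the unit changes little (10-16% at 0.5 SD, 29-35% at 0.8 SD).

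A separate simulation with 26 pairs and 50% men agrees: 16% and 35% for the three-group test at 0.5 and 0.8 SD. A direct Mann-Whitney test of male-male against female-female rejected in 20% and 44%.

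**Why the mixed versus same-gender contrast behaves differently.** With male share *q* and random pairing, mixed minus same-gender is (*g* + *p*) × [*q*²/(*q*² + (1 − *q*)²) − 1/2]. The bracket is 0 at *q* = 0.5, 0.16/0.52 − 0.5 = −0.19 at *q* = 0.4, and 0.09/0.58 − 0.5 = −0.34 at *q* = 0.3.

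**The case against.** The strongest reply is that the article does not fix the contrast. It names no unit, test or adjustment for the pair analysis. Its talk of heterogeneous and homogeneous groups fits a mixed versus same-gender comparison, which is nearly free of this problem near 50% men. A comparison within own gender would also fit the wording, and a condensed article may leave that to an analysis plan not shown. This stands in part: the confounded contrast is not the only possible one. But the text lists three pair types, describes a comparison between pair groups and supplies only unadjusted tests, so the plain reading is the confounded one. The mixed versus same-gender contrast is also no substitute. At 50% men it cancels an additive partner effect along with the own-gender gap, so it addresses only whether matching matters.

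The reply is also right that the stakes are low. The pair comparison is not among the listed endpoints, subgroup analyses are descriptive, and the section already admits a limitation, although it attributes this to the uncontrolled sex ratio rather than to own gender.

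A reader might infer that the trial relies on this comparison to decide whether training in pairs confounds its results. The article does not say so: the Training curriculum section defends pairing by the team's own unpublished comparison, the literature on learning by observation, and saved resources. Nor is the stated limitation about the sex ratio a mistake. Drawing partners at random would not guarantee adequate numbers of each pair type under skewed enrolment, and the article does not exclude that pairs are already formed that way.

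**Conclusion.** The point holds for the plain comparison of pair types, conditional on a gender gap. The bias in the male-male versus female-female difference is the whole own-gender gap, whether or not a test reaches significance. The three-group test then rejects in about 13-16% of trials at 0.5 SD and 31-38% at 0.8 SD, against 4-6% for the partner term once own gender is in the model.

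It would go too far to say that the analysis will show a pair effect where none exists. Without a gender gap the test keeps its level, and at 0.8 SD most trials of this size would still show nothing significant. The protocol supports the direction of the gap but not its size. The rates also assume random pairing, independent partners and no arm effect.

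The primary comparison and the sample size are not affected.

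**What to change.** In the Randomization section, replace the plain pair-type comparison with one that holds own gender fixed, in either of two forms:

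- compare men with a male versus a female partner, and women with a female versus a male partner; or
- model total training time and number of attempts on own gender, partner gender and arm, with pair as a cluster.

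Report the partner effect with a 95% CI and label it exploratory. The simulated model had own and partner gender only; arm and the pair cluster are added because real data may have an arm effect and correlated partners.

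The change costs about a paragraph and no new data: the planned gender comparison already needs each trainee's gender, and the mutual rating already links partners.

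The downside is precision. With 27 randomly formed pairs and 50% men, about 27 × 0.25 × 2 = 13.5 men have a male partner and 27 × 0.5 = 13.5 a female one. The 95% CI half-width for men alone is then about 1.96 × √(2/13.5) = 0.75 SD. With the two genders combined it is about 0.75/√2 = 0.53 SD. Within-pair correlation would change these widths. At 30% men only about 27 × 0.09 × 2 = 4.9 men would have a male partner, so the text should say that a small cell may be described without a test.
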